## Abstract

**Background:**

There is a worldwide epidemic of nonorganic gastrointestinal disorders (NOGDs), which are a class of disorders that cause various discomforts and ultimately progress into organic gastrointestinal diseases. Because of the unsatisfactory efficacy of Western medical treatments, traditional Chinese medicine (TCM) is becoming a promising complementary and alternative treatment to manage NOGDs.

**Objectives:**

To investigate the efficacy and safety of Hou Gu Mi Xi (HGMX), a newly developed dietary TCM formula, on the syndrome of spleen qi deficiency (SQD) in patients with NOGDs.

**Methods/Design:**

This study is a multicenter, randomized, double-blinded, parallel, and placebo-controlled trial that will last for 2 years. All qualified subjects with NOGDs and SQD will be included. The study population will be divided into the HGMX and placebo groups. To assess the efficacy of HGMX, we will mainly focus on changes in SQD symptoms scored by a Spleen Qi Deficiency Symptoms Grading and Quantifying Scale and evaluate changes in gastrin-17, the negative* Helicobacter pylori* conversion rate, body weight, body mass index, and gastroscopy findings. The safety of HGMX will be assessed by recording adverse events (AEs), severe AEs, treatment-related AEs and withdrawal due to AEs.

**Discussion:**

This trial is part of our study series that intends to validate the potential of HGMX in the management of chronic gastrointestinal diseases. This series of RCTs is the first committed to the evaluation of a dietary TCM formula and will hopefully establish an evidence-based clinical research model for dietary TCM formulas.

**Ethics:**

The protocol was approved by Ethics Committee of five research hospitals and was registered in Clinicaltrials.gov (NCT03019042).

## 1. Introduction

Chronic gastrointestinal diseases are one of the major health problems worldwide, with an incidence of approximately 60 to 70 million cases per year in the United States [1]. It was reported that up to 38.6 million clinic visits and 45.3 deaths per 100 thousand patients per year are due to chronic gastrointestinal diseases [1, 2]. Meanwhile, the incidence of chronic gastrointestinal diseases in China is 7.3‰, ranking fifth among all diseases [3]. Pathologically, chronic gastrointestinal diseases can be divided into organic gastrointestinal diseases and nonorganic gastrointestinal disorders (NOGDs); organic gastrointestinal diseases can develop from NOGDs, and a typical routine of pathological progression is from NOGDs to gastrointestinal metaplasia, atypical hyperplasia, precancerous lesions, and, ultimately, cancer [4, 5]. Therefore, although explicit epidemiological data for NOGDs remain unclear, the harm and burden of NOGDs are plausibly substantial.

NOGDs represent a series of disorders, mainly including chronic nonatrophic gastritis and functional gastrointestinal disorders listed in the Rome IV diagnostic criteria [6]. The symptoms of NOGDs are nontypical and may include gastrointestinal discomfort, such as nausea, stomach and abdominal distension, vomiting, acid reflux, diarrhea, and constipation, as well as systemic symptoms [6, 7]. Because it is challenging to cure most organic gastrointestinal diseases, such as atrophic gastritis, peptic ulcers, and gastric cancer, people are focusing on treating NOGDs and preventing progression, which would be more cost-effective than treating organic gastrointestinal diseases [8, 9]. However, the efficacy of most treatment options, predominantly anti-infection, anti-inflammation, and symptomatic treatments, in current Western medicine guidelines for NOGDs is unsatisfactory [10, 11].

Along with the development of medical science, traditional Chinese medicine (TCM) is playing an increasingly important role in the treatment of chronic gastrointestinal diseases, especially NOGDs [4]. The common symptoms of NOGDs mentioned above can be categorized as six syndromes in TCM—spleen qi deficiency (SQD), spleen-stomach deficiency cold, spleen deficiency and dampness, spleen deficiency and liver depression, liver and spleen imbalance, and liver qi stagnation—among which SQD is the most common, and the primary symptoms include stomach and abdominal distension, fatigue, weakness, loss of appetite, and diarrhea [12]. Spleen and qi are concepts in TCM that play roles in transiting food and water and maintaining activity, respectively. The TCM-based pathogenesis of spleen qi-deficient NOGDs is dysfunction in the spleen and stagnation of qi, which cause blood stasis, accumulation of phlegm, and food retention. Therefore, TCM therapy for NOGDs aims to invigorate and replenish qi, supported by nourishing the spleen, activating blood circulation, and removing damp evil, qi stagnation, and food retention [13].

Shen Ling Bai Zhu San, a classic Chinese herbal medicine formula, was originally described in* Tai Ping Hui Min He Ji Ju Fang* in the Nang Song Dynasty (1102 AD) [14]. Because of its effects of replenishing qi and nourishing the spleen, it has been used to treat SQD for thousands of years, especially for patients with NOGDs [15]. However, Shen Ling Bai Zhu San is a poor tasting powder that must be mixed with boiled water, which restricts its widespread use and long-term compliance.

On the basis of Shen Ling Bai Zhu San, a dietary TCM formula named Hou Gu Mi Xi (HGMX) is under development by Jiangzhong Pharmaceutical (group) Co., Ltd., Jiangxi, China, and had come into the market in September 2016, in which atractylodes (an herb that is forbidden in food) is replaced with orange peel. Consequently, HGMX is composed of ginseng (*Renshen*), tuckahoe (*Fuling*), coixenolide (*Yiyiren*), Chinese yam (*Shanyao*), lotus seed (*Lianzi*), amomum (*Sharen*), platycodon (*Jiegen*), white hyacinth bean (*Baibiandou*), licorice (*Gancao*), and orange peel (*Jupi*), all in the list of food in China. In this formula, ginseng, tuckahoe, coixenolide, and Chinese yam can invigorate spleen qi, remove dampness, and nourish our body, with the support of lotus seed, amomum, platycodon, white hyacinth bean, licorice, and orange peel. Theoretically, HGMX can replenish the spleen and stomach qi, remove the dampness and turbidity, and dissipate the qi stagnation such that the spleen qi can run normally and the damp evil can be removed, leading to the natural elimination of the symptoms of SQD. In addition, HGMX has been made into an oatmeal preparation and can be easily transformed into a rice paste with boiled water and can become our everyday breakfast. As a dietary formula, HGMX should be safe and show improved compliance with long-term intake.

However, the efficacy, safety, and compliance of HGMX are based solely on scientific theories and hypotheses, which are still under inspection. Therefore, we plan to conduct a postmarket, hospital-based, randomized controlled trial (RCT) to investigate the long-term efficacy and safety of HGMX on SQD in patients with NOGDs.

## 2. Methods/Design

### 2.1. Trial Design

This study is a multicenter, randomized, double-blinded, parallel-group, placebo-controlled trial that aims to determine whether HGMX is an effective and safe treatment for improving the symptoms of SQD in patients with NOGDs. The study population will be randomly divided into the HGMX group and the placebo group. The overall design is presented in Figure 1. The trial has been registered at Clinicaltrials.gov (No. NCT03019042). In order to guarantee standardized processes, precise judgment, and the safety of all participants, our study will be performed in accordance with the principles of Good Clinical Practices and the Declaration of Helsinki. We designed and reported our protocol according to Standard Protocol Items: Recommendations for Interventional Trials. [16].

### 2.2. Sites and Participant Recruitment

The potential participants will be recruited in three ways: oral promotion by researchers, hospital posters, and web page publicity. Patients with NOGDs will be recruited from five tertiary hospitals: First Affiliated Hospital of Nanchang University, Second Affiliated Hospital of Nanchang University, Jiangxi Hospital of Traditional Chinese Medicine, Nanchang Hospital of Integrated Traditional Chinese and Western Medicine, and Nanchang Hongdu Hospital of Traditional Chinese Medicine. Subjects who meet the inclusion criteria will be required to sign the informed consent form to show an overall understanding of study details prior to study participation.

### 2.3. Inclusion Criteria

Participants meeting all the following criteria will be included:Diagnosis with NOGDs by gastroscopy based on the Consensus on Integrated Traditional Chinese and Western Medicine in the Treatment of Chronic Gastritis and the ROMA IV criteria [6, 7], primarily including chronic nonatrophic gastritis, functional dyspepsia, and irritable bowel syndromeDiagnosis with SQD status according to the criteria in the Clinical Guidelines of New Drugs for Traditional Chinese Medicine [13]At least 14 years oldSign the informed consent form

### 2.4. Exclusion Criteria

Participants who report any of the following conditions will be excluded:Patients who have gastrointestinal disorders with organic pathologic changes, such as peptic ulcers, gastrointestinal erosions, gastroesophageal reflux disease, gastrointestinal hemorrhage or perforation, structural changes in gastrointestinal structure, gastrointestinal vascular diseases, ileus, or a benign tumorPregnant or breast-feeding womenPatients who have allergic history to the sample or sample componentsPatients with impaired liver or kidney function, including one of the following conditions: (a) total bilirubin, alanine transaminase, or aspartate aminotransferase > 2 upper limit of normal (ULN); (b) serum creatinine >2 ULNPatients with an obviously abnormal electrocardiogram (ECG), severe mental disorders, or any diagnosed malignancies;Patients who have taken drugs that can damage the stomach and intestine, such as nonsteroidal anti-inflammatory drugs, theophylline, oral antibiotics, or potassium supplements within 3 monthsPatients who have received any agents or other intervention for his/her gastrointestinal disorder within 3 monthsPatients who are unwilling to provide personal information or who cannot understand and sign the informed consent form

### 2.5. Randomization and Blinding

We used computer-based statistical analysis software to generate a randomization system that is saved as enciphered data. For allocation concealment, participants are grouped with a centralized randomization assignment. Except in cases of a severe adverse event (SAE), all the participants, medical care providers, data collectors, and outcome reviewers will be blinded before the data analysis. Hence, we established a randomization management center that is in charge of all processes related to random sequence generation, allocation concealment, and blinding. As a result, all the members of this center were excluded from any other processes in this study.

### 2.6. Interventions

Our participants are grouped into the HGMX group (experimental group) and the control group. In the HGMX group, participants will be treated with an oral dose of 30 g/day HGMX. Every 30 g of HGMX contains 10.1 g of herbal material (detailed components of HGMX are shown in Table 1) and 19.9g early rice and oats. Participants in the control group will receive the same dose of placebo, which consists of 66.7% early rice and 33.3% oats with the same preparation, packaging, labeling, and appearance but a slightly different taste and smell than the real HGMX. All subjects will be treated for a duration of 2 years (104 weeks). During follow-up, patients can be treated as necessary based on clinical guidelines for acute and chronic diseases (such as hypertension, diabetes, and osteoarthritis) that are not included in the exclusion criteria.

### 2.7. Outcomes

#### 2.7.1. Primary Outcome

The primary outcome is the change in the score of the Spleen Qi Deficiency Symptoms Grading and Quantifying Scale (SQD scale), which was derived from a classic scale in the Clinical Guidelines of New Drugs for Traditional Chinese Medicine to Validate Spleen Qi Deficiency Symptoms [13]. The SQD scale consists of 17 items that assess (1) stomach distension, (2) abdominal distension, (3) physical fatigue and weakness, (4) mental fatigue and taciturnity, (5) loss of appetite, (6) abnormal stools, (7) stomach pain, (8) stomach tightness, (9) abdominal pain, (10) acid reflux, (11) belching, (12) nausea and vomiting, (13) abnormal bowel sounds, (14) powerless defecation, (15) sallow complexion, (16) loss of taste and hypodipsia, and (17) facial and limb edema. Items 1-6 focus on primary symptoms, and the other items focus on secondary symptoms. The scale assesses all the symptoms of SQD, including the duration of each episode (0-3 points, available for items 1-2 and 7-9), the severity (0-3 points, not available for item 13), and the number of episodes per day (0-4 points, except 0-3 for item 5) and per week (0-5 points). The score of each item will be used to calculate the total score, with 2 points for primary symptoms and 1 point for secondary symptoms. As a result, the total score ranges from 0 to 292, and higher scores indicate more severe symptoms. Compared with the original scale, we have added four symptoms (items 1, 7, 10, and 11) and defined 5 primary symptoms. In addition, we assess not only the severity, which is included in the former scale, but also the duration and the number of episodes per day and per week for these symptoms. For more details, see Table S1 in the supplementary material.

#### 2.7.2. Secondary Outcomes

Changes in gastrin-17 (ng/L) levels in order to determine whether the intervention can improve gastric function were observedChanges in body weight (kg) and body mass index (kg/m^2^) were observedQuantitative changes were observed by gastroscopy

#### 2.7.3. Safety Outcomes

Incidence of adverse events (AEs), including abnormal ECG and dramatic changes (indicated by a value outside 2 × the lower or upper normal reference interval) in alanine transaminase (U/L), aspartate aminotransferase (U/L), total bilirubin (*μ*mol/L), direct bilirubin (*μ*mol/L), indirect bilirubin (*μ*mol/L), or serum creatinine (*μ*mol/L). In addition, doctor-observed and patient-reported AEs are also included.SAEs are those AEs that could result in treatment in the hospital, a longer in-hospital stay, transfer to an intensive care unit, disability, life-threatening complications, and death.Treatment-related AEs defined as those AEs fully meet the following condition [17]: (1) the occurrence time is logically related to treatment administration; (2) the adverse effects cannot be interpreted by cointerventions and comorbidities; (3) the adverse effects should relieve or disappear when the treatment is withdrawn; (4) the relation is supported by definitively pharmacological or phenomenological mechanism.Withdrawal was due to AEs.

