### 2.8. Study Follow-Up and Outcome Assessments

The durations of follow-up and treatment are equal at 2 years. In our study, all participants will be evaluated 8 times: at baseline and in weeks 2, 4, 8, 26, 52, 78, and 104. After the qualified participants sign the informed consent form, they will document the characteristics of their own symptoms in the baseline case report form (CRF) and then record the baseline (first visit) physical and laboratory examination data. In weeks 2 and 4, participants will complete the Spleen Qi Deficiency Symptoms Grading and Quantifying Scale (SQD scale) and a physical examination. In weeks 8, 26, 52, 78, and 104, an ECG and laboratory examination, including routine blood, urine, and stool tests, are required. Gastrin-17 and* Helicobacter pylori* will be assessed at both weeks 52 and 104. Gastroscopy will be performed at only baseline and the last visit.  Table 2 provides an overview of the study procedures.

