### 2.9. Sample Size Estimation

This RCT is a superiority study. From an overall consideration, we will restrict the type I error (*α*) and type II error (*β*) to 0.05 and 0.2, respectively. The variation between groups and the combined standard deviation of the primary outcome were estimated at 6.0 and 13.0, respectively, based on the results of a preliminary observational study. In addition, a maximum rate of 20% withdrawal or loss to follow-up was adopted. Therefore, with the corresponding sample size estimation equation [18] and the consideration of funding constraints, we computed an expected sample size of 200, with 100 in each group.

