### 2.10. Statistical Analysis

We will conduct an interim analysis at week 52 and a final analysis at week 104 with the help of the statistical software SPSS v23.0.

Specifically, an intention-to-treat analysis will be adopted for primary outcomes, while the per-protocol analysis will be performed as a sensitivity analysis. The last observation carried forward method will be used for missing data due to loss to follow-up. Continuous and categorical variables will be analyzed by t-test (or analysis of variance) and Pearson chi-squared test, respectively. In addition, continuous variables with a skewed distribution will be compared with the nonparametric rank-sum test. A P value ≤ 0.05 will indicate statistical significance for all the comparisons mentioned above, and group sequential method will be used to adjust the significant boundary for multiple t-test [19]. Subgroup analysis stratified by type of NOGDs (nonatrophic gastritis versus functional gastrointestinal disorders) and infection of* Helicobacter pylori* (yes versus no) will be performed. Furthermore, an analysis based on safety data set with no imputation will also be conducted. The incidence of AEs in the two groups will be compared using the Pearson chi-squared test, and all the AEs will be described in detail.

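### Section 2.7.3 counts any abnormal ECG as an adverse event without reference to baseline, so minor abnormalities admitted at entry can be counted as events in both arms; the same gap exists for direct and indirect bilirubin

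*Protocol article*

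**What the plan says.** Three parts of the protocol article bear on this.

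- **Outcome (2.7.3).** The first safety outcome is "Incidence of adverse events (AEs), including abnormal ECG and dramatic changes" in six laboratory tests: ALT, AST and total bilirubin, followed by "direct bilirubin (*μ*mol/L), indirect bilirubin (*μ*mol/L), or serum creatinine (*μ*mol/L"). A laboratory change counts as dramatic when it is "indicated by a value outside 2 × the lower or upper normal reference interval". The ECG criterion carries no qualifier of severity and no comparison with baseline.
- **Entry (2.4).** Participants are excluded for "total bilirubin, alanine transaminase, or aspartate aminotransferase > 2 upper limit of normal (ULN"), for serum creatinine above the same multiple, or for an ECG that is obviously abnormal. Direct and indirect bilirubin have no entry limit.
- **Schedule and test (2.8, Table 2, 2.10).** Table 2 places the ECG, liver and kidney tests at baseline, and section 2.8 repeats them: "In weeks 8, 26, 52, 78, and 104, an ECG and laboratory examination". Section 2.10 then states: "The incidence of AEs in the two groups will be compared using the Pearson chi-squared test".

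**The concern.** The entry rule and the event rule for the ECG do not meet. Entry tolerates abnormalities short of obvious ones, while the event rule is triggered by any abnormality. A participant who enters with a minor finding and never changes therefore satisfies the event wording at week 8. The baseline ECG that would tell this participant apart from a new case is collected, but the definition does not use it.

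The comparison at stake is the overall adverse event incidence, the only between-group safety test that section 2.10 specifies. A background of unchanged findings, equal on average in the two arms, raises both rates and moves the ratio toward 1. In a safety comparison that is the less cautious direction. Long-term safety is one of the trial's stated aims.

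**Working it through.** The article gives no figure for ECG or adverse event rates, so there is nothing of the plan's own to reproduce. The check is a comparison of thresholds, followed by an illustration on assumed rates.

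**Step 1. Entry ceiling against upper event threshold.**

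| Finding | Highest level admitted (2.4) | Event when (2.7.3) | Can already be met at entry? |
|---|---|---|---|
| ALT, AST, total bilirubin | 2 × ULN | above 2 × ULN | No |
| Serum creatinine | 2 × ULN | above 2 × ULN | No |
| Direct, indirect bilirubin | no limit of their own | above 2 × ULN | Possible |
| ECG | anything short of obviously abnormal | abnormal | Yes |

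The cap on total bilirubin restrains the sum of the two fractions. Whether it also keeps each fraction below twice its own limit depends on laboratory reference limits that the article does not give. The table covers the upper side only.

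**Step 2. Level or change.** The laboratory criterion is labelled a change but defined by a level. Two invented cases show the effect. A move from 1.9 to 2.05 × ULN is a rise of 2.05/1.9 = 1.08, or 8%, and counts. A move from 0.5 to 1.9 × ULN is a rise of 1.9/0.5 = 3.8-fold and does not.

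**Step 3. Dilution for the ECG.** Let b be the share with a pre-existing abnormality that persists and is counted, and p the rate of new abnormality among the rest. Then

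observed rate = b + (1 − b) × p.

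Assumed: p = 5% and 15%, two-sided 0.05. The arm size of 100 comes from section 2.9, and 80 is 100 × (1 − 0.20) under its withdrawal allowance. Power is the normal approximation for two proportions, with q̄ the mean of the two observed rates q1 and q2:

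power = Φ{ [ (q2 − q1) − 1.96 × √(2q̄(1 − q̄)/n) ] / √( [q1(1 − q1) + q2(1 − q2)]/n ) }.

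At b = 10%, q1 = 0.10 + 0.90 × 0.05 = 0.145 and q2 = 0.10 + 0.90 × 0.15 = 0.235. With n = 100 and q̄ = 0.19, the standard errors are 0.0555 (null) and 0.0551 (alternative). So power = Φ[(0.090 − 0.1087)/0.0551] = Φ(−0.34) = 36.7%.

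| b | Observed rates | Risk ratio | Risk difference | Power, 100 per arm | Power, 80 per arm |
|---|---|---|---|---|---|
| 0% | 5.0% v 15.0% | 3.00 | 10.0 points | 65.6% | 56.0% |
| 5% | 9.75% v 19.25% | 1.97 | 9.5 points | 47.9% | 39.9% |
| 10% | 14.5% v 23.5% | 1.62 | 9.0 points | 36.7% | 30.4% |
| 20% | 24.0% v 32.0% | 1.33 | 8.0 points | 24.1% | 20.1% |
| 30% | 33.5% v 40.5% | 1.21 | 7.0 points | 17.4% | 14.8% |

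With assumed new-event rates of 5% and 20% and 100 per arm, b = 10% lowers the risk ratio from 4.0 to 1.93 and power from 90.0% to 64.8%.

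**The case against.** The other side has real arguments.

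- **Incidence normally means new occurrences, and coding rules for pre-existing findings often sit in the full protocol or the case report form instructions.** This may well be what the authors intend. But the rule is stated here, and its wording names a state for the ECG where it speaks of changes for the laboratory tests. Five hospitals could apply it differently.
- **Treatment-related events are reported separately, with conditions on timing and on other explanations.** An unchanged finding should fail those conditions. That protects the treatment-related category, but the test in section 2.10 is named for adverse event incidence as a whole.
- **Randomisation balances pre-existing findings.** It does, so no arm is favoured systematically. Balance does not prevent dilution of the ratio or the loss of power.
- **The illustration overstates the effect.** This stands in part. The risk difference shrinks only from 10 to 9 points at b = 10%. The tested outcome also includes laboratory, doctor-noted and patient-reported events, so the ECG share of it is unknown. The rates are assumed, and every pre-existing abnormality is taken to persist and be counted.

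A reader might also infer that any out-of-range laboratory value is an event, or that admitting values up to 2 × ULN makes those values events. The documents do not support this. The trigger is twice the limit, and for ALT, AST, total bilirubin and creatinine the matching entry ceiling means an admitted participant is not already an event on the upper side. Nor do the documents show that a real safety difference would be hidden; that depends on a prevalence they do not give. Finally, large rises below 2 × ULN need not be lost, because a doctor may still record them as adverse events.

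**Conclusion.** The point holds for the ECG. As written, a minor abnormality present at entry and unchanged can count as an adverse event in either arm. It is a possible route for direct and indirect bilirubin. It does not hold at the upper limit for the other four laboratory tests, where what remains is a mismatch between a label that says change and a definition that uses a level. Replacing that level with a change-from-baseline threshold would be closer to a preference than a correction.

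The direction is clear: higher incidence in both arms and a risk ratio nearer to 1. The size is not known. The fall in the risk ratio from 3.0 to about 1.6, and in power from about 66% to 37%, belongs to an ECG-only comparison with assumed new-event rates of 5% and 15%, 10% pre-existing abnormality and 100 per arm. It is not an estimate for this trial. The wording should be changed because the rule is stated and the remedy is nearly free.

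**What to change.** In section 2.7.3, state that an ECG or laboratory finding counts as an adverse event only if it is new or worse than that participant's own baseline. Unchanged findings present at entry are then listed as baseline findings and not counted as events. Add tables of the shift from baseline to worst post-baseline result, by arm, for the ECG and the six laboratory tests.

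For ALT, AST, total bilirubin and creatinine this alters nothing at the upper limit, since crossing it already means a rise above the entry value. The change acts on the ECG and the two bilirubin fractions. The shift tables would also show large rises that stay below 2 × ULN, without a second threshold.

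The cost is a slightly longer definition and a little more programming. No added visit or test is needed, because Table 2 already schedules these measurements at baseline.

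### The treatment-related AE rule shuts out fatal and irreversible events by definition, and the laboratory AE threshold, read literally, flags normal values

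*Protocol article*

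**What the plan says.** Section 2.7.3 of the protocol article names four safety outcomes: AEs, SAEs, treatment-related AEs and withdrawal due to AEs.

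- **Relatedness.** The rule is "Treatment-related AEs defined as those AEs fully meet the following condition". Criterion 1 is plausible timing. Criterion 2 is no explanation by co-interventions or comorbidities. Criterion 3 is that "the adverse effects should relieve or disappear when the treatment is withdrawn". Criterion 4 is that "the relation is supported by definitively pharmacological or phenomenological mechanism".
- **SAEs.** The listed outcomes include "transfer to an intensive care unit, disability, life-threatening complications, and death".
- **Laboratory AEs.** A dramatic change in ALT, AST, total, direct or indirect bilirubin, or creatinine is "indicated by a value outside 2 × the lower or upper normal reference interval".

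Three other places bear on these rules. Section 2.4 excludes patients at entry on an upper bound only, > 2 ULN, for total bilirubin, ALT, AST and creatinine. Section 2.8 makes treatment and follow-up the same length, 2 years. Section 2.13 withdraws discontinued participants, including those with an SAE, without a laboratory examination.

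**The concern.** Requiring all four criteria turns recovery on withdrawal from supporting evidence into a condition of entry. An event that kills or permanently harms can never show it. The treatment-related AE outcome would then be silent on the harms a reader most wants attributed, and a low count could not be told apart from an effect of the definition.

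The laboratory rule may err in the other direction. If the lower arm means below twice the lower limit, unremarkable results become AEs in both arms. They would enter the overall AE incidence, which section 2.10 compares by chi-squared test. Non-differential false events of this kind dilute a real contrast.

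**Working it through.** The plan states no figure on this point, so there is none to reproduce. The relatedness rule is a matter of logic and the laboratory rule a matter of algebra.

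**(a) Relatedness.** Related = C1 and C2 and C3 and C4. The status of criterion 3 by type of event:

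| Event | Criterion 3 | Result under the rule |
|---|---|---|
| Relieved after withdrawal, and observed | met | can be related |
| Death | cannot be met | never related |
| Permanent disability | cannot be met | never related |
| Laboratory abnormality in a discontinued participant | no examination at withdrawal (2.13) | status undefined |
| Event near week 104 | no follow-up after treatment ends (2.8) | status undefined |
| Event with product continued | withdrawal not tested | status undefined |

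The second and third rows need no assumed number. They follow from the criteria and from the SAE outcomes listed in the same section. The last three rows show that the schedule often leaves criterion 3 unobservable, and the rule gives no instruction for that.

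**(b) Laboratory bound.** Let L = LLN, U = ULN and r = L/U. The literal rule flags x < 2L or x > 2U. The normal values flagged are those from L up to min(2L, U), so

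share of the normal interval flagged = (min(2r, 1) − r) / (1 − r).

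For r = 0.2 this is (0.4 − 0.2)/(1 − 0.2) = 0.25.

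For the share of normal *persons*, assume Gaussian values with L and U as the 95% limits: mean (L + U)/2, SD (U − L)/3.92. With U = 1 and r = 0.2, the mean is 0.6 and the SD is 0.8/3.92 = 0.204. The cut at 0.4 lies at z = −0.98, and the share among values inside the interval is 14.6%.

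The article gives no reference limits, so r is an assumption and is varied:

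| LLN/ULN (assumed) | Normal interval flagged | Normal persons flagged (Gaussian) |
|---|---|---|
| 0 | 0% | 0% |
| 0.05 | 5% | 2% |
| 0.1 | 11% | 4% |
| 0.2 | 25% | 15% |
| 0.3 | 43% | 38% |
| 0.4 | 67% | 76% |
| 0.5 or more | 100% | 100% |

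Two other readings of the lower arm are possible: below half the LLN, or no lower arm at all, as in section 2.4. Under either, 0% of normal values are flagged at every r.

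**Consistency with section 2.4.** Four of the six analytes appear in both places (ALT, AST, total bilirubin, creatinine); direct and indirect bilirubin do not. For the four, a participant with a normal result between L and 2L passes screening and, on the literal reading, already meets the AE threshold at baseline.

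**The case against.** The strongest reply is that little rests on relatedness. In a randomised, blinded trial the causal evidence on safety is the comparison of all AEs between arms. A death still counts as an AE and as an SAE, section 2.10 tests AE incidence, and all AEs are to be described. This stands. A reader might infer that the definition guarantees a finding of safety; the documents do not support that, because three of the four safety outcomes never use the rule.

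A reader might also infer that criterion 4 demands a proven mechanism nobody has, given the Introduction's statement that "the efficacy, safety, and compliance of HGMX are based solely on scientific theories and hypotheses". That goes too far. Criterion 4 also accepts phenomenological support, and the Discussion refers to animal and clinical research on the parent formula. Nor must every AE with the product continued be scored as failing criterion 3; an untested condition could be set aside. The text does not say which, and that is the defect.

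The criteria come from a cited source that is not shown, and a full protocol may grade causality. But the article states the combining rule itself and requires all four, so this is a stated rule and not an omission.

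On the laboratory bound, the wording is loose. A result inside the normal range is hardly a dramatic change, and the authors may have meant half the lower limit or only > 2 ULN. This stands too: the defect is a badly worded threshold, and false AEs follow only if it is applied as written. The inference that most participants would be flagged, or that a real difference would be hidden, needs reference limits, value distributions and correlations across analytes and visits that the article does not give.

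**Conclusion.** Both points hold, within limits.

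- **Relatedness.** Fatal and irreversible events are excluded by definition from one of four safety outcomes, and unassessable events have no defined status. This rests on the text alone. All-cause AE, SAE and AE-withdrawal counts are not affected.
- **Laboratory threshold.** Read literally, it flags some normal values for every analyte with a lower limit above zero and none where that limit is zero. It also disagrees with section 2.4 for four of the six analytes. The effect on AE incidence cannot be fixed from the article: it runs from none to every normal value as LLN/ULN goes from 0 to 0.5, and is nil if the authors intended either alternative reading.

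The treatment-related AE count cannot be interpreted as defined, and the laboratory rule cannot be applied uniformly across five hospitals. Both should be corrected before the data are unblinded.

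**What to change.** 1. **Relatedness, for analysis and reporting only.** Classify each AE, blinded to arm, as at least possibly related on criteria 1 and 2. Use criteria 3 and 4 only where they can be assessed, to grade certainty. State that a criterion that cannot be assessed does not rule out relatedness, and name fatal and irreversible events as examples. Report each grade by arm beside all-cause AEs.
2. **Laboratory AEs.** Replace the present wording with one unambiguous bound that cannot flag a value inside the reference range. Reconcile it with the > 2 ULN bound in section 2.4, say what applies to direct and indirect bilirubin, and apply it to post-baseline values where the participant was not already beyond the bound at baseline.

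The cost is definition wording and CRF coding, with no change to treatment or visits. The downside is that more events will be reported as possibly related than under the present rule. Grading by arm lets the reader see how much of that is weak attribution.
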